## Quality assurance

### Dummy run/RT QA

Before the initiation of a trial centre each site has to perform a “dummy run” to demonstrate that the centre complies with the specific study requirements for delineation, IMRT planning, dose distribution and treatment delivery. For the dummy run a planning CT will be sent by the IMRT-planning QA centre to each participating institution and the results (structures, isodoses, DVH’s) are evaluated by the QA centre. When the dummy run is successfully completed, a site will be allowed to recruit patients for the study. The first 3 patients of a trial site will be checked for centrally QA.

## Study treatment

### Chemotherapy

The chemotherapy of the ESCALOX trial will contain a platinum based protocol. The application of Cisplatin 20 mg/m^2^/d in week 1 (d1-5) and 5 (d29-33) as well as Cisplatin given in a weekly schedule with 40 mg/m^2^/d q d7 (max. 6 cycles) is allowed. In the case of impairment of renal function due to cisplatin the switch to carboplatin with AUC 2 in a weekly application scheme is allowed.

### Radiation therapy

The use of linear accelerator or a tomotherapy machine with nominal photon energy ≥ 6 MV is allowed. Electron beams are prohibited. The recommended photon energy is 6 or/and 10 MV. Only IMRT with SIB-technique is allowed. All fields of the IMRT-plan will be treated on every treatment day. It is recommended to avoid beams through sensitive structures (OARs) i.e. the eyes. The radiotherapy course has to be completed with 35 fractions in 55 days (with holidays, weekends, planned interruptions: day off, machine maintenance).

### Re-treatment planning

In all cases a second and a third planning CT should be done after 15 and 25 fractions of radiotherapy. Re-Planning has to be done if changes of the GTV_PT+LN_ are clinically significant. If there is > 5% loss of body weight and/or > 1 cm difference in any set-up parameter during treatment a re-planning CT should be performed and the treatment plan has to be adapted. The use of image guidance is recommended.

### Planning priorities

The planning target volumes (SIB 56, SIB 70 and (SIB 77) SIB 80.5) should be delineated in the way that there is a sufficient level of homogeneous tissue for adequate dose homogeneity within the PTVs.For the OAR constraints the biological equivalence dose for 2 Gy (EQD2) using the α/β – value of 3 is calculated.

The PTV prescription dose followed by the OAR-constraints (see Table 2) has the highest priority.

**Table 2 Tab2:** ESCALOX - trial Dose constraints for Organs at Risk (OAR)

OAR	Necessity for planning	accepted dose [EQD2]
Spinal cord (PRV: Myelon + 5 mm)	Mandatory	D_max_ < 50 Gy_2_ or No more than 1 cm^3^ > 45 Gy_2_
Brachial plexus	Mandatory	60 Gy_2_
Brainstem	Mandatory	D_max_ < 54 Gy_2_ or no more than 1 cm^3^ > 54 Gy_2_
Optical nerve	Mandatory	Dmax < 54 Gy_2_
Mandible	Recommended	D_max_ < 70 Gy_2_ or no more than 1 cm^3^ > 70 Gy_2_
Glottis (outside PTV)	Recommended	2/3 < 50 Gy_2;_ D_mean_ < 45Gy_2_
Gl. parotis	Recommended	D_mean_ < 26 Gy_2;_ D_50_ < 30 Gy_2_ 20 cm^3^ of both < 20 Gy_2_

a) Dose prescription of SIB 80.5, SIB 70, SIB 56.

b) OAR (spinal cord, brainstem, Glottis, mandible; in this order).

c) Further aim of the planning: total dose to the salivary glands as low as possible.

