***GTV)***
**:** The description of the gross tumor volume is based on CT and optionally MRI scan, endoscopic and clinical examinations as well as additional imaging.

A lymph node should be classified as involved, if it has/there arediameter ≥ 1 cm (jugulo-digastric lymph nodes >1.1–1.5 cm) in the first echelon of the tumordiameter ≤ 1 cm with spherical shape in the first echelon of the tumorlymph nodes containing necrotic areasmultiple (minimal 3) lymph nodes of the ipsilateral neck of the primary tumor.

All these lymph nodes should be delineated for GTV.

***Clinical target volume (CTV)*** is defined as the GTV plus regions classified to be at risk for microscopic spread. The extension of this volume is determined by the radio-oncologist.

**CTV 70** is defined as GTV of the primary tumor plus 1 cm and GTV of the involved lymph nodes plus 0.5 cm but for cranio-caudal direction also 1 cm (for control group and for experimental group).

**CTV 56** is defined as elective lymph node levels (for control group and for experimental group).

***Planning target volume (PTV)*** here deemed as SIB 56 and SIB 70 for experimental and control group.

**SIB 56** is defined as an additional set-up margin around CTV 56 in all directions to compensate for morphological changes (i.e. weight loss), set-up deviation and internal organ motion.

0.5 cm as safety margin is recommended for the upper cervical structures and 0.7 cm for the lower cervical structures. Exceptions are the direct neighborhood of critical organs as the spinal cord or other organs at risk.

A skin sparing of 0.3 cm is recommended unless the tumor invades near the skin or e.g. into the sternocleidomastoid muscle.

In addition, the set-up margin should be defined according to the results on set-up error for IMRT at each participating center.

The **SIB 70** will be derived from the CTV 70 (automatically contoured margins by the planning system) as described above. The SIB 70 has to be adapted by hand at each planning CT slice to organs at risk and anatomical boundaries.

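### Target prescription is ranked ahead of the spinal cord and brainstem limits that Table 2 labels Mandatory, and the brainstem Dmax clause has no effect

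*Protocol article*

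**What the plan says.** In the protocol article, Study treatment, Planning priorities, the governing sentence is: "The PTV prescription dose followed by the OAR-constraints (see Table 2) has the highest priority". The list printed after Table 2 sets out the order. It begins "a) Dose prescription of SIB 80.5, SIB 70, SIB 56", continues "b) OAR (spinal cord, brainstem, Glottis, mandible; in this order", and ends with sparing of the salivary glands as a further aim.

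Table 2 has a column headed Necessity for planning. Spinal cord, brachial plexus, brainstem and optic nerve are marked Mandatory there; mandible, glottis and parotid are marked Recommended. The next column gives the accepted dose in EQD2. For the cord, entered as "Spinal cord (PRV: Myelon + 5 mm", it is "D_max_ < 50 Gy_2_ or No more than 1 cm^3^ > 45 Gy_2". For the brainstem it is "D_max_ < 54 Gy_2_ or no more than 1 cm^3^ > 54 Gy_2".

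The section on target volumes and dose prescription also bears on the point. After recommending set-up margins it adds: "Exceptions are the direct neighborhood of critical organs as the spinal cord or other organs at risk". It further requires SIB 70 to be edited by hand, slice by slice, with regard to organs at risk. Trial organization/coordination and Dummy run/RT QA provide for central quality assurance of delineation and planning.

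**The concern.** A planner needs to know which side yields when the full prescription and an organ limit cannot both be met. For spinal cord and brainstem one expects the organ limit to prevail. The sentence and the list give the opposite order: cord and brainstem come first among the organs, but below every target level, including the elective SIB 56. The Mandatory label points the other way without saying what it requires.

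At stake is patient safety beside two critical organs, in both arms, because SIB 70 and SIB 56 are common to both. The brainstem row adds a smaller problem: it appears to set a maximum dose, but the way its two clauses are joined removes that maximum. No endpoint, sample size or analysis is affected.

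**Working it through.** **1. The order against the label.** Two readings of Mandatory are possible.

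- *The limit must be met.* Then a plan that breaks the cord or brainstem limit does not comply, whatever the list says, and the section gives two conflicting rules.
- *The organ must be contoured and considered in planning.* Then nothing in the section qualifies the order (a) before (b), and the prescription may override the limit.

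The text needs correcting on both readings, but for different reasons.

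**2. Does the order matter at the doses used?** Inputs: 35 fractions (Radiation therapy); 80.5, 70 and 56 Gy at 2.3, 2.0 and 1.6 Gy per fraction (Abstract, Methods); alpha/beta of 3 for organ limits (Planning priorities).

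EQD2 = D × (d + 3) / (2 + 3)

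- SIB 56: 56 × 4.6 / 5 = 51.52 Gy
- SIB 70: 70 × 5.0 / 5 = 70.00 Gy
- SIB 80.5: 80.5 × 5.3 / 5 = 85.33 Gy

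Compared with the limits:

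- Cord Dmax of 50 Gy: SIB 56 is above it by 51.52 − 50 = 1.52 Gy, and SIB 70 by 20 Gy.
- Brainstem level of 54 Gy: SIB 56 is below it by 54 − 51.52 = 2.48 Gy; SIB 70 is above it by 16 Gy.

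The same limits as physical dose in 35 fractions come from solving D(D/35 + 3)/5 = L, that is D = 35 × (−3 + √(9 + 20L/35)) / 2:

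- L = 50: D = 54.77 Gy. From 70 Gy, dose must fall by 15.23 Gy (15.23/70 = 21.8%).
- L = 54: D = 57.98 Gy. From 70 Gy, dose must fall by 12.02 Gy (12.02/70 = 17.2%).

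Where the distance between target edge and organ allows that fall-off, there is no conflict. Where it does not, the stated order decides, and as printed it favors the target.

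**3. The brainstem row.** Call the clauses A (Dmax < 54) and B (no more than 1 cm³ above 54). If A holds, 0 cm³ exceeds 54, so B holds too. Since A implies B, the rule A or B is the same as B alone. The row therefore reduces to no more than 1 cm³ above 54 Gy. A brainstem with 0.9 cm³ above 54 Gy and a Dmax of 55, 70 or 85.3 Gy passes in each case. Replacing *or* with *and* would reduce the row to Dmax < 54, which makes the volume clause redundant instead. So changing the conjunction alone cannot make both clauses work.

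**The case against.** The strongest defense is that Mandatory binds. Table 2 is titled as dose constraints, its third column gives an accepted dose, and Mandatory contrasts with Recommended. A planner could reasonably treat the label as overriding the list. This stands as a possible reading, and it rules out saying flatly that the plan lets target dose exceed cord tolerance. It does not remove the inconsistency with the list.

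Second, the prescription applies to targets already cut back near organs at risk, and only oral cavity, oropharynx and hypopharynx tumors are eligible. Conflicts are therefore rarer than the dose figures alone suggest. But trimming does not say which side yields at the trimmed edge. Table 2 addresses overlap only for one organ, "Glottis (outside PTV".

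Third, central quality assurance may stop an unsafe plan. A reader might infer that reviewers would have no ground to reject one. The documents do not support that: plan-acceptance criteria and point-dose ceilings may stand in the full protocol, which an article condenses. For the same reason, the brainstem row should not be read as showing that the trial permits unlimited dose in 1 cm³; it shows only that the printed Dmax clause does nothing. A small-volume tolerance is itself a legitimate clinical choice.

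Fourth, a reader might infer greater danger in the experimental arm because of the 80.5 Gy level. SIB 70 and SIB 56 are defined alike in both arms. Before trimming, SIB 80.5 lies well inside the SIB 70 edge: around the primary, 1.0 + 0.5 = 1.5 cm to 1.0 + 0.7 = 1.7 cm. No arm difference can be claimed.

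**Conclusion.** The point holds as a fault in a stated rule. Planning priorities places the prescription before the spinal cord and brainstem limits, and this either contradicts the Mandatory label or, on the weaker meaning of that label, allows target dose to override the limits. The doses make the order relevant: SIB 70 is 20 Gy EQD2 above the cord Dmax and 16 Gy above the brainstem level, and SIB 56 is 1.5 Gy above the cord Dmax. These figures assume the stated alpha/beta of 3 and 35 fractions. They show that a conflict can arise, not how often or by how much a limit would be exceeded; the documents give no basis for either. The redundancy of the brainstem Dmax clause follows from logic alone and is a wording fault. Correcting the order is a cheap improvement for patient safety.

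**What to change.** In Planning priorities, for both arms:

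- State that the Table 2 limits for spinal cord and brainstem take precedence over the SIB 80.5/70/56 prescription, that the prescription ranks next, and that the organs marked Recommended follow it. Amend the governing sentence and the lettered list to match.
- State that Mandatory in Table 2 means the limit must be met. This would also bind the other rows with that label, so the sponsor should confirm that this is intended or relabel them.
- Reword the brainstem row so that its Dmax clause has an effect: either a plain Dmax < 54 Gy, or the 1 cm³ allowance above 54 Gy together with a separate, higher Dmax. Any such value is the sponsor's clinical choice; the documents do not supply one.

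The cost is a few lines of text and, in some plans, slightly lower target dose next to the cord or brainstem.

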### Target volumes and dose prescription

#### Target volume definitions and delineation for control and experimental group (main study)

***Gross tumor volume***
*(*
***GTV)***
**:** The description of the gross tumor volume is based on CT and optionally MRI scan, endoscopic and clinical examinations as well as additional imaging.

A lymph node should be classified as involved, if it has/there arediameter ≥ 1 cm (jugulo-digastric lymph nodes >1.1–1.5 cm) in the first echelon of the tumordiameter ≤ 1 cm with spherical shape in the first echelon of the tumorlymph nodes containing necrotic areasmultiple (minimal 3) lymph nodes of the ipsilateral neck of the primary tumor.

All these lymph nodes should be delineated for GTV.

***Clinical target volume (CTV)*** is defined as the GTV plus regions classified to be at risk for microscopic spread. The extension of this volume is determined by the radio-oncologist.

**CTV 70** is defined as GTV of the primary tumor plus 1 cm and GTV of the involved lymph nodes plus 0.5 cm but for cranio-caudal direction also 1 cm (for control group and for experimental group).

**CTV 56** is defined as elective lymph node levels (for control group and for experimental group).

***Planning target volume (PTV)*** here deemed as SIB 56 and SIB 70 for experimental and control group.

**SIB 56** is defined as an additional set-up margin around CTV 56 in all directions to compensate for morphological changes (i.e. weight loss), set-up deviation and internal organ motion.

0.5 cm as safety margin is recommended for the upper cervical structures and 0.7 cm for the lower cervical structures. Exceptions are the direct neighborhood of critical organs as the spinal cord or other organs at risk.

A skin sparing of 0.3 cm is recommended unless the tumor invades near the skin or e.g. into the sternocleidomastoid muscle.

In addition, the set-up margin should be defined according to the results on set-up error for IMRT at each participating center.

The **SIB 70** will be derived from the CTV 70 (automatically contoured margins by the planning system) as described above. The SIB 70 has to be adapted by hand at each planning CT slice to organs at risk and anatomical boundaries.

#### Pre-Study: Special Definition of dose escalated planning target volume (SIB 77.0) for the pre-study group in step-wise recruitment

**Dose escalated volume (deemed as SIB 77.0):** The dose escalated volume is defined as the gross tumor volume (GTV) of the primary tumor (PT) and all involved lymph nodes (LN) with a minimal axial diameter > 2 cm. At critical structures (e.g. mucosal sites, vessels, skin) the GTV is reduced by 0.3 cm (inner margin). Treatment planning will be performed without set-up error for the SIB 77.0.

All lymph nodes detected as involved with a minimal axial diameter of 2 cm will be also included as SIB 77.0.

For definition of SIB 70 and SIB 56 see above (Planning target volume (PTV) here deemed as SIB 56 and SIB 70).

##### Special Definition of dose escalated planning target volume (SIB 80.5) for the experimental arm (group A)

**Dose escalated volume (deemed as SIB 80.5**)**:** The definition for the SIB 80.5 uses the same guideline as for SIB 77 in the pre-study. Planning will be performed without set-up error for SIB 80.5.

Description of delineation of SIB 70 and SIB 56 is given above.

The dose constraints for organs at risk (OAR) are shown in Table 2.

### Evaluation of therapy outcome

CT or MRI of the head and neck is performed at the time of screening and then at every follow-up visit (4 month interval during the first two follow-up years) using the RECIST-criteria version 1.1 to assess efficacy of chemo-irradiation.

## Statistics

### Sample size calculation

Sample size calculations are based on the Log-rank test for superiority of the experimental arm over the comparator arm in LRC-survival over two years. The two-year LRC-survival is expected to be about 60% in the comparator group and about 75% in the experimental group. When the sample size in each group is 125, the one sided Log-rank test will have power of about 80% to detect the assumed difference at the 0.05 level. Therefore, 250 patients need to be recruited in the trial, 125 in each arm.

Due to missing alternative therapy concepts in non-resectable LAHNSCC, the expected compliance rate will be over 95%. Missing values will be conservatively treated: In the control arm, missing values will be imputed by the longest observed loco-regional survival time. In the experimental arm, missing values will be set to the time of censoring.

Because of the pre-study requirements of the BfS the pre-study will include 20 patients. These 20 patients are on top of the calculated 250 patients for the whole trial.

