**Discussion:**

The primary endpoint of the pre-study is acute radiation induced toxicity. Primary endpoint of the main trial is 2-year-LRC. By using the dose escalation up to 80.5 Gy to the GTV of the primary tumor and lymph nodes > 2 cm a LRC benefit of 15% at 2 years should be expected. The ESCALOX trial is supported by Deutsche Forschungsgemeinschaft (DFG); Grant No.: MO-363/4-1.

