**Fig. 1 Fig1:**
[figure not shown]
ESCALOX - Trial scheme

IMRT or VMAT will be performed to apply the RT as simultaneous integrated boost. The ESCALOX trial enrols patients with LAHNSCC of the oral cavity, oropharynx or hypopharynx. Patients will be treated by the University Departments of Radiation Oncology and Radiation Therapy in Germany.

The primary endpoint of the pre-study as recommended by the German Federal Office of Radiation Protection (BfS) will be the assessment of acute toxicity. The primary endpoint of the main study is the local-regional control (LRC) at 2 years.

The secondary endpoints are disease-free survival (DFS), progression-free survival (PFS), overall survival (OS), acute and late radiation effects, adverse events, tumor hypoxia status investigated by 18-F-FMiso-PET.

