### Statistical methods

#### Primary efficacy endpoint analysis for the main part of the trial

The primary efficacy endpoint of the trial, LRC-survival over two years, will be tested for superiority of the experimental arm over the comparator arm using the one-sided Log-rank test at the 0.05 significance level on the ITT set. LRC-survival is defined as time to local relapse or death calculated from start of radiotherapy.

The corresponding hypotheses are:

H0: Se(t) ≤ Sc(t) vs. Ha: Se(t) > Sc(t),

Se and Sc denote the two-year LRC-survival in the experimental arm and in the control arm respectively.

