## Discussion

The addition of concomitant chemotherapy to radiotherapy, irrespective of fractionation schedule, increases overall survival by 12 months [11]. In the 2011 meta-analysis of the MACH-NC-group the additional effect of chemotherapy concerning HR of death was calculated to be 0.88 [5]. 5-FU and cisplatin or cisplatin mono based concomitant chemo-irradiation gained the best survival benefit compared with other cytostatic drugs [4].

The chemotherapy treatment of the ESCALOX trial will use cisplatin weekly with 40 mg/m^2^/day or cisplatin in the 1^st^ and 5^th^ week of the radiotherapy given on 5 days with a cumulative dose of 200 mg/m^2^ in both schedules. At this time there is still controversial debate on the best cisplatin regimen weekly vs. three weekly [12] and on the number of cycles [13].

In spite of the significant clinical benefit from concomitant radio-chemotherapy, there is still the need for further improvement. Two and 5 year loco-regional control rates after combined therapy are given from 40% to 65%. These disappointing numbers indicate that most loco-regional recurrences are observed within the first 2 years after treatment and that overall survival considerably declines with further follow up [14]. The latter is also the result of a high likelihood of non-cancer deaths related to the smoking and drinking habits of many head and neck cancer patients [15]. The overall survival in the same trials at 2 and 5 years ranges between 50% to 65% and 35% to 45, respectively. The absolute gain of 5-y-OS is 6.5–8% due to concomitant chemotherapy [4, 5].

In clinical trials testing chemotherapy in combination with identical radiotherapy regimens in all arms of the study, loco-regional control does not correlate well with overall survival. In contrast, in randomized trials addressing radiation dose or fractionation schedules loco-regional control has been shown to be a reliable surrogate marker of overall survival [14]. Any improvements in overall survival by dose escalation of radiotherapy with constant overall treatment time has to be attributed to an increase in clonogenic tumor cell kill within regions receiving an escalated dose, and in this way caused by better loco-regional control.

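### The planning rates of 60% and 75% look like loco-regional control rates, but the tested endpoint also counts death, so the document does not support the stated 80% power for that endpoint

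*Protocol article*

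**What the plan says.** In the protocol article, Statistics, Sample size calculation: "The two-year LRC-survival is expected to be about 60% in the comparator group and about 75% in the experimental group". The same paragraph continues: "When the sample size in each group is 125, the one sided Log-rank test will have power of about 80" percent, at the 0.05 level.

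Primary efficacy endpoint analysis: the comparison is made "using the one-sided Log-rank test at the 0.05 significance level on the ITT set", and "LRC-survival is defined as time to local relapse or death calculated from start of radiotherapy".

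Other sections describe the endpoint and the effect without death:
- Study design: "The primary endpoint of the main study is the local-regional control (LRC) at 2 years".
- Abstract, Discussion: "a LRC benefit of 15% at 2 years should be expected".
- Background, Hypothesis of the trial: the 15% improvement within two years is again one of loco-regional control.

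The outcome evidence stands in two places. The Discussion reports: "Two and 5 year loco-regional control rates after combined therapy are given from 40% to 65" percent; and "The overall survival in the same trials at 2 and 5 years ranges between 50% to 65% and 35% to 45, respectively". Hypothesis of the trial cites 2-year overall survival of 90-94% from two studies in locally advanced disease. The document gives no rate of death without relapse.

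**The concern.** LRC and freedom from relapse or death are different endpoints. A patient who dies without relapse is an event only for the second, so that rate can never exceed overall survival. Against the Discussion's 2-year survival range of 50-65%, 75% is above the whole range. A rate of 60% is possible only near its top, and then only if almost no survivor has relapsed. As an LRC rate, by contrast, 60% sits inside the Discussion's 40-65%, and the 15-point difference is exactly the LRC gain that the Abstract and the hypothesis claim. The figures therefore appear to have been chosen for LRC and then labelled LRC-survival.

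Two things are at stake. If local dose escalation does not prevent deaths without relapse, those deaths pull the hazard ratio towards 1, and the stated power is too favourable. And a significant result on relapse or death could not be reported as the 15% LRC benefit that the Abstract announces.

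**Working it through.** **Inputs from the document.** 125 per arm, one-sided 0.05 (z = 1.645), two-year rates 60% and 75%, comparison over two years.

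**Input not in the document.** q, the 2-year probability of death without relapse. It is assumed equal in both arms and independent of relapse, with constant hazards, and is shown from 5% to 20%.

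**Formulas.** Sc and Se are the two-year event-free rates in the control and experimental arms.
- HR = ln(Se)/ln(Sc)
- Events by two years: D = 125 × [(1 − Sc) + (1 − Se)]
- Schoenfeld power = Φ(½√D × |ln HR| − 1.645)
- Freedman power = Φ(√D × (1 − HR)/(1 + HR) − 1.645)

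**Step 1: the plan's own figure.** HR = ln 0.75 / ln 0.60 = 0.563. D = 125 × (0.40 + 0.25) = 81.25. Schoenfeld gives 82.7% and Freedman 80.9%. A simulated log-rank test cut at two years gives 82.1%. The stated figure of about 80% is reproduced.

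**Step 2: read 60% and 75% as LRC rates.** The composite rates become Sc = 0.60(1 − q) and Se = 0.75(1 − q).

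| q | Composite, control vs experimental | HR | Events | Power, Schoenfeld / Freedman |
|---|---|---|---|---|
| 5% | 57.0% vs 71.3% | 0.603 | 89.7 | 77% / 76% |
| 10% | 54.0% vs 67.5% | 0.638 | 98.1 | 72% / 71% |
| 15% | 51.0% vs 63.8% | 0.669 | 106.6 | 67% / 66% |
| 20% | 48.0% vs 60.0% | 0.696 | 115.0 | 62% / 61% |

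Simulation cut at two years agrees: 76.6%, 71.7%, 66.7% and 62.0%.

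**Step 3: keep the full 15-point gap on the composite.** This applies if relapse-free deaths take the same number of points off both arms. For 50% vs 65%, HR = ln 0.65 / ln 0.50 = 0.622 and D = 125 × (0.50 + 0.35) = 106.25. Power is 79.0% (Schoenfeld) or 77.7% (Freedman).

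**Step 4: use follow-up beyond two years.** The accrual period is not stated. Assuming three years of uniform accrual and counting all follow-up, simulated power is about 85%, 80% and 74% at q = 10%, 15% and 20%. On the same basis it is about 94% with no relapse-free deaths, so the loss relative to that remains.

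**Step 5: take the label literally.** If 60% and 75% are composite rates, the implied LRC rates are 0.60/(1 − q) and 0.75/(1 − q):
- q = 5%: 63.2% vs 78.9%, a gain of 15.8 points
- q = 10%: 66.7% vs 83.3%, a gain of 16.7 points
- q = 15%: 70.6% vs 88.2%, a gain of 17.6 points

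From 10% on, the control LRC lies above the Discussion's 40-65%. At every q shown, the required LRC gain is larger than the 15 points claimed.

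**The case against.** The strongest reply is that the plan is consistent by its own label. The planning rates, the hypotheses and the test all use the term LRC-survival, which is defined as relapse or death, and the stated power follows from those rates. That stands: there is no arithmetic error, and that the rates are LRC rates is an inference, not something the document says.

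A reader might go further and infer any of the following. The documents do not support them.
- *That 75% is impossible.* The Discussion's 50-65% comes from past combined-therapy trials, not from an escalated arm, and the Background's 90-94% would leave room for 75%. Nor can the 90-94% be set aside because the Background also reports LRC of 86-100%: that range comes from other studies, in non-selected tumor stages. What remains is a conflict that the document leaves open.
- *That relapse-free death within two years is shown to be frequent.* The Discussion links non-cancer deaths to the decline in survival with longer follow-up and gives no two-year rate. The entry criteria also exclude serious concomitant disease and a life expectancy under one year.
- *That 80% power is certainly not delivered.* The loss depends on the assumed q and on cutting follow-up at two years. It is small at q = 5%, and small if the 15-point gap survives on the composite.

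Counting death in the primary endpoint is a legitimate choice. Replacing it with a cause-specific endpoint would be debatable, and nothing here requires it.

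**Conclusion.** The point holds as a mismatch between endpoint and planning rates, not as a miscalculation. The document justifies a 15-point gain only for LRC but tests relapse or death, and it offers no support for 60% vs 75% on that composite. If the figures are LRC rates, power at two years is about 77% with 5% relapse-free deaths and falls to about 62% with 20%. This rests on equal, independent relapse-free death in both arms, constant hazards and a two-year cut, and the death rates are assumed. The difference in endpoint naming needs none of these assumptions.

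**What to change.** Name one primary endpoint in the same words in the Abstract, Hypothesis of the trial, Study design, Sample size calculation and Primary efficacy endpoint analysis. While doing so, settle whether the event is local relapse, as the definition has it, or loco-regional relapse, as the endpoint's name implies.

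If relapse or death is kept:
- Restate its two-year planning rates and power with an explicit relapse-free death rate, and reconcile them with the survival figures in the Background and the Discussion.
- State whether follow-up beyond two years counts in the test.
- Report loco-regional failure as a secondary analysis by cumulative incidence with death as a competing event. The secondary-endpoint section already foresees that estimator for competing risks.
- Do not describe a result on the composite as an LRC benefit.

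The cost is a few rewritten sentences and probably a less favourable stated power. No extra patients are asked for.
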